### Criteria for withdrawal

Subjects can leave the study at any time for any reason if they wish to do so without any consequences. Patients that drop-out from the trial within the first 3 months from baseline will be replaced and not be part of the intention to treat analysis. Patients that drop-out from the trial later on will not be replaced by new patients and will be asked for an early-end of treatment. The investigator can withdraw a subject from the study for urgent medical reasons, such as (but not limited to): occurrence of a concomitant disease in which leuprorelin is contra-indicated, pregnancy, need of treatment that is contra-indicated during the trial (such as estrogens), lost-to-follow up or, by the opinion of the treating physician, high need for surgical volume reducing treatments. If a patient that is registered on the waiting list receives a transplant offer, this patient will also be withdrawn from the trial.

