### Concomitant medication

For massive PLD, somatostatin analogues are currently the only evidence-based treatment. Therefore, somatostatin analogues should be used, tried, or have been considered before inclusion in the AGAINST-PLD trial. Patients are thus allowed to use a somatostatin analogue during the trial (see inclusion criteria, Table 1). During the study, start or stop of somatostatin analogues as well as surgical procedures to reduce liver volume should be avoided unless there are important reasons to do so, because this could interfere with the assessment of the primary outcome, liver growth.

Use of estrogen- and or progesterone containing medication is not allowed during the trial period, because it could interfere with the effect of the study treatment. Blood pressure treatment is targeted below 130/80 mmHg with RAAS-inhibitors as the first-choice agents. Calcium vitamin D (500 mg/800 IE) will be prescribed to all patients in the study to prevent osteoporosis.

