### Outcome parameters

#### Primary outcome

Liver growth (%/y), calculated over the first 18 months of the trial and compared between the direct start group (on treatment) and delayed start group (on standard of care), b–e versus b–c, Fig. 3.

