### Statistics

#### Statistical analysis

Analyses are performed after completion of the study. For the primary outcome, liver growth during the first 18 months of the trial compared between direct and delayed starters, an unpaired t-test will be used. In case of missing data, last information will be used adjusted for the duration of follow up. For questionnaires, the delta in scores during the first 18 months of the trial will be compared between direct and delayed starters. To compare liver growth within individuals before and during treatment, a paired t-test will be used. Adverse events will be categorized and the number of adverse events per category will be compared between direct and delayed starters using an unpaired t-test.

For all primary and secondary analyses, we will perform pre-defined sensitivity analysis to adjust for age, disease type (ADPKD vs. ADPLD), total liver volume at baseline, total kidney volume at baseline, use of somatostatin analogues, and test differences in treatment effects among these variables (interaction). In a sensitivity analysis we will test for differences in the outcome variables between the first 18 months of the trial and the second 18 months of the trial in the direct start group, using a breakpoint analysis. All analyses will be performed based on an intention to treat principle. As a sensitivity analysis, we will perform a per-protocol analysis.

In an additional analysis we will explore whether liver growth is linear and whether the liver growth rate during treatment is different in the first 6 months of treatment compared to the 12 months thereafter, using a multiple mixed model.

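### The withdrawal criteria merge stopping leuprorelin with leaving the study, so follow-up to month 18 can be lost selectively in the direct-start arm and the intention-to-treat analysis is compromised

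*Protocol article*

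**What the plan says.** All references are to the protocol article.

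- **Criteria for withdrawal, level of exit.** "The investigator can withdraw a subject from the study for urgent medical reasons, such as (but not limited to): occurrence of a concomitant disease". The list continues: "in which leuprorelin is contra-indicated, pregnancy, need of treatment that is contra-indicated during the trial (such as estrogens". What the woman leaves is the study, not the study drug.
- **Criteria for withdrawal, later drop-outs.** "Patients that drop-out from the trial later on will not be replaced by new patients and will be asked for an early-end of treatment". The content of that early-end assessment is not described. One sentence thus links leaving the trial with ending treatment.
- **Concomitant medication.** "Use of estrogen- and or progesterone containing medication is not allowed during the trial period". A woman who comes to need hormones therefore meets a listed reason for leaving the study.
- **Statistical analysis.** "All analyses will be performed based on an intention to treat principle". Gaps are handled as follows: "In case of missing data, last information will be used adjusted for the duration of follow up".
- **Primary outcome.** "Liver growth (%/y), calculated over the first 18 months of the trial", compared between direct and delayed start.
- **MRI scans; Data collection and management.** Liver MRI is at screening and months 6, 18, 24 and 36. DEXA is at baseline, halfway and end of study.

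The article describes no status in which a woman is off leuprorelin but still attends visits.

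**The concern.** A contra-indication to leuprorelin, pregnancy or a need for estrogens bears on whether she can take the drug. None of them by itself prevents a visit, a questionnaire or the recording of adverse events, and often it does not prevent a scan.

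The loss need not be balanced. The rule covers both arms, but before month 18 only direct starters are exposed, so any trigger that leuprorelin itself causes can occur only there. The article names such risks: osteoporosis and cardiovascular events with long estrogen depletion (Efficacy–safety ratio), both given as contra-indications in Table 1, and menopausal complaints for which add-back hormones are not allowed.

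At stake are the month-18 growth comparison, the adverse-event comparison (a secondary outcome), the PLD-Q comparison and the month-18 bone-density comparison. With 36 women, a few selective losses matter. An analysis plan cannot recover visits that were never made.

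**Working it through.** **1. The plan's own figure.** Sample size calculation gives a control mean of 5.8% per 18 months, an SD of 2.8% doubled to 5.6%, growth fully stopped (difference 5.8%), alpha 0.05 (two-sided assumed), power 80%, and 20% drop-out.

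n per arm = 2 × [5.6 × (1.960 + 0.842) / 5.8]² = 14.63, so 15 per arm and 30 in total. Then 30 × 1.2 = 36, as stated. (Dividing instead, 30 / 0.8 gives 38.) The drop-out allowance covers lost precision; it does not address selective loss.

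**2. What remains for a woman who leaves between months 6 and 18.**

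| Item | Scheduled data between baseline and month 18 | Consequence |
|---|---|---|
| Liver MRI | month 6 only | the 6-month slope stands for 18 months, unless she is rescanned on exit |
| DEXA | none | no scheduled post-baseline value |
| Questionnaires | month 6 | no month-18 change score |
| Adverse events | up to exit | later events not counted; numbers compared by t-test with no adjustment for follow-up time stated for that comparison |

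The early slope is not a safe substitute. The article itself plans to explore whether growth is linear and whether the first 6 months on treatment differ from the next 12.

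**3. Size of the distortion in liver growth (illustration).** Assumptions, not figures from the document: 18 women per arm; m direct starters stop and leave at month 6 with zero growth so far; off drug they grow at the control rate for the remaining 12 months; all other direct starters have zero growth.

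- Last-information rule: each leaver is scored at zero growth, so the difference stays 5.8% per 18 months.
- Full follow-up: difference = 5.8 × [1 − (m/18) × (12/18)].

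| m of 18 | Full follow-up | Shown by the rule | Overstatement | No month-18 DEXA (m/18) | Patient-years lost (m × 1.0 of 27) |
|---|---|---|---|---|---|
| 1 | 5.59% | 5.8% | 3.8% | 6% | 4% |
| 2 | 5.37% | 5.8% | 8.0% | 11% | 7% |
| 3 | 5.16% | 5.8% | 12.5% | 17% | 11% |
| 4 | 4.94% | 5.8% | 17.4% | 22% | 15% |

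Patient-years in the arm: 18 × 1.5 = 27. Each leaver at month 6 loses 1.0 year.

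**4. Does fuller follow-up raise power?** Unpaired t-test, SD 5.6%, two-sided 0.05:

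- 18 vs 18 with the full 5.8% difference: 85.5%.
- 13 vs 16 evaluable (7 lost, about 20% of 36, of whom 5 assumed to be direct starters): 76.2%.
- 18 vs 18 with those five followed but off drug from month 9 and growing at the control rate: difference 5.8 × [1 − (5/18) × (9/18)] = 4.99%, power 73.9%.

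The third case is the fair comparator for the second, and it is no higher. The second is also too pessimistic about numbers, because the last-information rule keeps women who have a month-6 scan.

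**The case against.** The strongest defence has five parts.

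- **The rule is permissive.** The investigator can withdraw a woman; nothing makes exit automatic for the drug-related reasons. Only a transplant offer leads to certain withdrawal. This stands, and a reader should not infer that every woman with a safety event must leave. But discretion over who leaves an open-label trial is itself a possible source of bias.
- **Intolerance is not listed.** This also stands. It can enter only through need of estrogens, the open-ended list or the woman's own choice. The article also provides non-hormonal treatment for side effects and a gynecologist at every site.
- **Intention to treat is still possible.** A reader might infer that it cannot be delivered. The document does not support that: later drop-outs are not replaced, and the last-information rule keeps those with a month-6 scan in the primary analysis. The sharper departure from the principle is a different sentence, on early drop-outs: "Patients that drop-out from the trial within the first 3 months from baseline will be replaced and not be part of the intention to treat". That is a separate matter from the one raised here.
- **The triggering event can be counted.** It occurs before exit, so the adverse-event comparison is not confined to women who tolerated the drug. What is lost is what happens afterwards.
- **The article is condensed.** The full protocol may define the early-end assessment and further follow-up. This limits how firmly one can say that data will not be collected. It does not remove the point, because the level of withdrawal is stated here, not omitted.

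A claim that the rule costs power, or that the fix restores it, fails on step 4 of the working.

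**Conclusion.** The concern holds in this form: the article states withdrawal from the study for reasons that concern only leuprorelin or its restrictions, gives no route for follow-up off drug, and so sits badly with its own intention-to-treat statement. Where the rule is used, the loss can be selective, because drug-caused triggers before month 18 exist only in the direct-start arm.

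The primary analysis survives, but it leans on extrapolating early on-drug slopes. The overstatement of about 4% to 17% rests on the assumed 1 to 4 leavers at month 6, zero growth on drug and regrowth at the control rate; it would be smaller with an exit scan close to month 18 or slower regrowth. Bone density and later adverse events have no comparable fallback. The frequency of such withdrawals is unknown, so the size is an illustration and not a forecast.

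**What to change.** Reconcile Criteria for withdrawal with Statistical analysis:

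- Define discontinuation of study drug and withdrawal from the study as two separate events.
- State that women who stop leuprorelin, or cannot start it, remain in the already scheduled visits (MRI, DEXA, questionnaires, adverse events) in their randomised arm through at least month 18, if they consent and where medically feasible.
- Leave the clinical reasons for stopping drug, and the handling of surgery, transplant and pregnancy, to the investigators.

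**Cost.** One protocol amendment and a line in the consent form. No new visit type is needed, because these visits are already planned for all 36 women. The intention-to-treat effect will include off-drug time and be diluted, so no power gain should be claimed. The per-protocol sensitivity analysis already planned can show the effect in women who adhered. The benefit is less bias in the month-18 comparison and more complete safety data.

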### Statistics

#### Statistical analysis

Analyses are performed after completion of the study. For the primary outcome, liver growth during the first 18 months of the trial compared between direct and delayed starters, an unpaired t-test will be used. In case of missing data, last information will be used adjusted for the duration of follow up. For questionnaires, the delta in scores during the first 18 months of the trial will be compared between direct and delayed starters. To compare liver growth within individuals before and during treatment, a paired t-test will be used. Adverse events will be categorized and the number of adverse events per category will be compared between direct and delayed starters using an unpaired t-test.

For all primary and secondary analyses, we will perform pre-defined sensitivity analysis to adjust for age, disease type (ADPKD vs. ADPLD), total liver volume at baseline, total kidney volume at baseline, use of somatostatin analogues, and test differences in treatment effects among these variables (interaction). In a sensitivity analysis we will test for differences in the outcome variables between the first 18 months of the trial and the second 18 months of the trial in the direct start group, using a breakpoint analysis. All analyses will be performed based on an intention to treat principle. As a sensitivity analysis, we will perform a per-protocol analysis.

In an additional analysis we will explore whether liver growth is linear and whether the liver growth rate during treatment is different in the first 6 months of treatment compared to the 12 months thereafter, using a multiple mixed model.

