### Patient selection

Detailed inclusion criteria are given in Table 1, of which the most important are:Female patients, pre-menopausalAnti Mullerian Hormone (AMH) level > 0.3 (a lower level indicates upcoming menopause)Age 18–45 years (inclusive)PLD with a very large liver for age, based on the upper 10% of volumes in our PLD registry (n = 1600) [27].One historical MRI or CT scan, performed 1–5 years before baseline, available to calculate liver growth before start of the studyOngoing liver growth, confirmed using a historical scan (a) obtained in routine clinical care and the scan at screening (b) with the liver volume in ml from scan b–a > 0.Use of a somatostatin analogue (only proven effective therapy currently available) or reason not to use such drug (e.g. not tolerated, ineffective, not available)

**Table 1 Tab1:** Overview of in- and exclusion criteria for the AGAINST-PLD study

Inclusion criteria	
Female	
Diagnosis of PLD (presence of > 10 cysts)	
Age 18–45 (inclusive) years	
Very large liver for age:	
18–30 y hTLV > 2.0 L/m	
30–35 y hTLV > 2.2 L/m	
25–40 y hTLV > 2.5 L/m	
40–45 y hTLV > 3.0 L/m	
1 historical MRI or CT scan of the liver available, made 5-1 y before baseline	
Ongoing liver growth, confirmed using the historical scan and MRI scan at screening	
Use of somatostatin analogues OR a reason not to use them (e.g. tried in de past but stopped because of side effects, not effective, no acces, patient does not want to)	
Voluntary written informed consent	

Exclusion criteria	
Post menopausal status or (vasomotor) symptoms indicating upcoming menopause	
AMH < 0.03 ng/ml at screening	
Active desire to have children, pregnancy or breast-feeding	
Contra-indications for leuprorelin, such as cardiovascular disease or osteoporosis	
Liver transplantation expected within 1.5 years	
Use of oral estrogen or progesterone containing medication	
Contra-indications for MRI	
Chronic use of immunosupressive agents	
Severe hypertension (systolic pressure ≥ 160 and/or diastolic pressure ≥ 100 mmHg)	
Clinically significant uncontrolled medical condition that, in the opinion of the investigator, would put the safety of the patient at risk though participation, or which would affect efficacy or safety analysis, such as, but not limited to, recurrent cholangitis, recurrent ascites, hepato-venous outflow obstruction, (history of) depression	
Participation in other interventional studies at the same time	

Exclusion criteria related to the historical MRI/CT scan	

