### Randomization

Participants will be randomized 1:1 between direct and delayed start (after 18 months) of treatment using an online Interactive Response System (IXRS) tool, stratified for somatostatin analogue use (yes/no) and age (< 40 and ≥ 40 years).

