#### Exploratory outcomes

Height adjusted liver volumes, compared between the direct and delayed start group after 18 monthsEstradiol, progesterone, AMH, LH and FSH levels at baseline, 6, 18, 24 and 36 monthsDifference between acute and chronic effects of treatment on liver growth as assessed by a mixed models analysis comparing liver growth rate in the first 6 months of treatment compared to the next 12 months of treatment.
With respect to tolerability:Quality of life, using the validated 36-Item Short Form Health Survey (SF-36) and the Beck Depression Inventory II (BD-II) questionnairesMenopause related complaints: using the Menopause Specific Quality of Life (MENQOL) questionnaireBone density: T-score on Dual Energy X-ray Absorptiometry (DEXA) scans will be compared between direct start group and delayed start group after 18 months.
For patients with polycystic kidney disease (PKD) also:Kidney growth (%/y) calculated over the first 18 months of the trial compared between direct and delayed start groupKidney growth rates within individuals compared before treatment and during treatmentDifferences between acute and chronic effects of treatment on kidney growthRenal function decline before and during treatment.

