### Sample size calculation

In our own DIPAK 1 trial [13], the mean liver growth rate in patients meeting the inclusion criteria was + 5.8% ± 2.8% per 18 months. Since the information on liver growth rate in this specific group is scarce, we conservatively doubled the SD to ensure enough power. We aim at fully stopping liver growth. Using β = 80%, α = 0.05, and incorporating a 20% drop-out rate, inclusion of 36 patients is needed to show this effect. In other proof-of-concept studies in PLD, similar numbers of patients were included [28, 29].

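### The primary test is an unadjusted t-test that omits the two stratification factors and the pre-trial growth rate; it is valid but may give up some efficiency in a 36-patient trial.

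*Protocol article*

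**What the plan says.** All references are to the protocol article.

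- **Primary outcome.** "Liver growth (%/y), calculated over the first 18 months of the trial", compared between the direct-start and delayed-start arms.
- **Statistical analysis.** The test is fixed: "compared between direct and delayed starters, an unpaired t-test will be used". No covariate is named for it. The same section pre-defines sensitivity analyses, for all primary and secondary analyses, that adjust for age, disease type, baseline liver volume, baseline kidney volume and somatostatin analogue use. Pre-trial growth is not in that list.
- **Randomization.** Allocation is 1:1, "stratified for somatostatin analogue use (yes/no) and age (< 40 and ≥ 40 years".
- **Patient selection, Table 1.** Every patient needs "1 historical MRI or CT scan of the liver available, made 5-1 y before baseline". The difference from the screening scan must be above zero, so each patient enters with a measured pre-trial growth rate (a–b in Fig. 3).
- **Secondary outcomes.** The a–b rate is used only in the within-patient comparison of the direct-start arm.
- **Exploratory outcomes.** Height-adjusted liver volume is compared between arms after 18 months. For bone density, "T-score on Dual Energy X-ray Absorptiometry (DEXA) scans will be compared between direct start group and delayed start group after 18 months". Baseline DEXA and MRI are both collected (Data collection and management).

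**The concern.** Stratifying on analogue use and age implies that the sponsor expects them to be related to liver growth. If they are, an analysis that ignores them uses a standard error that is too large. Pre-trial growth is on the same kind of scale as the outcome and is an obvious candidate predictor. Leaving it out of every between-arm model also means that a chance imbalance between the arms in how fast livers were already growing is not corrected in any between-arm estimate.

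At stake is precision that costs no extra patient or scan. The disease is rare, about 30 evaluable patients are expected, and the sample size has no reserve at the planning standard deviation.

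**Working it through.** **1. Reproducing the planned sample size.** Inputs from Sample size calculation: "the mean liver growth rate in patients meeting the inclusion criteria was + 5.8% ± 2.8% per 18 months"; "we conservatively doubled the SD to ensure enough power", giving 2 × 2.8 = 5.6; "We aim at fully stopping liver growth", giving a difference of 5.8 points per 18 months; 80% power; α = 0.05 (taken as two-sided); 20% drop-out.

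n per arm = 2 × (1.960 + 0.842)² × (5.6/5.8)² = 14.63, rounded up to 15, or 30 in total. Then 30 × 1.2 = 36, which is the stated figure. The plan is therefore sized for an unadjusted two-sided comparison by the normal approximation.

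**2. Power of the planned t-test.** The standardised difference is d = 5.8/5.6 = 1.036. Exact power uses the noncentral t with noncentrality d√(n/2) and 2n − 2 degrees of freedom:

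| Evaluable per arm | Power |
|---|---|
| 18 (no loss) | 85.5% |
| 15 | 78.2% |
| 14.4 (36 × 0.8 / 2) | 76.4% |
| 14 | 75.1% |

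**3. Power of the adjusted model.** The model contains arm, two binary stratification factors and one continuous covariate (historical growth). With 14 per arm the residual degrees of freedom are 26 − 3 = 23. R² is the share of outcome variance that the three covariates explain. The documents give no value, so a range is assumed. Strata are taken as balanced. Chance imbalance in the continuous covariate inflates the variance by about (2n − 3)/(2n − 4) = 25/24.

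Noncentrality = d/√(1 − R²) × √(14/2 × 24/25).

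| Assumed R² | Residual SD, 5.6√(1 − R²) | t-test | Adjusted | Change |
|---|---|---|---|---|
| 0 | 5.60 | 75.1% | 73.0% | −2 |
| 0.09 | 5.34 | 75.1% | 76.9% | +2 |
| 0.16 | 5.13 | 75.1% | 80.1% | +5 |
| 0.25 | 4.85 | 75.1% | 84.3% | +9 |

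A simulation of the same model (20,000 runs per setting, same effect in all patients) gave adjusted power of 73%, 77%, 80% and 85%, in agreement.

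**4. If past growth predicts only untreated growth.** The same simulation was run with historical growth related to the outcome in the control arm alone. At control-arm R² of 0.09, 0.16 and 0.25, adjusted power was 74%, 75% and 76%, against about 75% for the t-test. The gain then all but disappears.

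**5. Type I error.** In a simulation of 30 evaluable patients with stratified blocks, the t-test rejected a true null in about 4.5% of runs when the strata explained 10% of the variance, and in 3.4% when they explained 20%. The adjusted model stayed at about 5%. The t-test is therefore not anti-conservative.

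**6. Adding baseline liver volume as a further covariate.** With log total liver volume also in the model, simulated adjusted power at 14 per arm was 70%, 75%, 78% and 82% for R² of 0, 0.09, 0.16 and 0.25. At equal total R² this is about 2 points below the smaller model.

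**The case against.** The strongest reply is that this is a preference and not an error. The t-test is valid after stratified randomisation and matches the sample size calculation. The standard deviation was deliberately doubled: at the observed 2.8, power with 14 per arm exceeds 99.9% for the stated effect, and efficiency hardly matters. Adjustment can also cost power. With uninformative covariates it loses about 2 points, and the protocol itself calls growth data in this group scarce. Historical growth comes from CT or MRI over an interval of 1 to 5 years and is restricted to values above zero, both of which may weaken its relation to on-trial growth. All of this stands, and it limits the point to one of efficiency with an uncertain gain.

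A reader might infer more than the documents support:

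- *That the plan ignores the stratification factors and baseline volume.* It does not. Age, analogue use and baseline liver volume are in the pre-defined adjusted sensitivity analysis. Only pre-trial growth is absent from every between-arm model.
- *That the primary estimate is biased.* Randomisation protects it.
- *That baseline is unused elsewhere.* Growth in %/y is already scaled to the starting volume, and the PLD-Q is compared as a change.
- *That the bone-density comparison has almost no power.* The documents give no spread or expected loss of T-score, so no power figure can be attached. It is also an exploratory outcome.

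What the reply does not remove is that the decisive test is fixed as unadjusted, although the design stratifies on two factors and collects a third relevant covariate on everyone.

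**Conclusion.** The point holds as a possible loss of efficiency in a valid, if anything conservative, primary test. Its size cannot be derived from the documents. Over an assumed R² of 0 to 0.25, moving to the adjusted model changes power by about −2 to +9 points.

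These figures rest on 14 evaluable patients per arm, the doubled standard deviation, complete stopping of growth as the effect, and the same covariate relation in both arms. The gain shrinks towards nothing if historical growth predicts only untreated growth. Fourteen per arm is itself a working figure, because the protocol replaces very early drop-outs and uses the last available information for later ones.

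The change is worth making because the worst-case loss is small, the data are already collected, and the analysis would then follow the randomisation.

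The secondary point is modest: comparing month-18 T-score and height-adjusted liver volume without their baseline values leaves between-woman variation in the comparison that can be removed at no cost.

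**What to change.** - Make the primary analysis a linear model of 18-month growth rate on arm, somatostatin analogue use, age group (cut at 40 years) and historical growth rate (a–b). Report the adjusted difference with its 95% confidence interval.
- Keep the unpaired t-test as a sensitivity analysis. Baseline liver volume need not enter the primary model, because the outcome is already a percentage rate; it can stay in the existing adjusted sensitivity analysis.
- Compare 18-month height-adjusted liver volume and DEXA T-score adjusted for the baseline values already collected.

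The cost is a change of wording in the statistics section, fixed before any comparison of the arms is seen, including at the planned interim analysis. No patients or scans are added. The statistical price is 3 degrees of freedom (26 to 23 at 14 per arm) and roughly 2 points of power if the covariates explain nothing.

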**Methods:**

The AGAINST-PLD study is an investigator-driven, multicenter, randomized controlled trial. Institutional review board (IRB) approval was received at the University Medical Center of Groningen and will be collected in other sites before opening these sites. Thirty-six female, pre-menopausal patients, with a very large liver volume for age (upper 10% of the PLD population) and ongoing liver growth despite current treatment options will be randomized to direct start of leuprorelin or to 18 months standard of care and delayed start of leuprorelin. Leuprorelin is given as 3.75 mg subcutaneously (s.c.) monthly for the first 3 months followed by 3-monthly depots of 11.25 mg s.c. The trial duration is 36 months. MRI scans to measure liver volume will be performed at screening, 6 months, 18 months, 24 months and 36 months. In addition, blood will be drawn, DEXA-scans will be performed and questionnaires will be collected. This design enables comparison between patients on study treatment and standard of care (first 18 months) and within patients before and during treatment (whole trial). Main outcome is annualized liver growth rate compared between standard of care and study treatment. Secondary outcomes are PLD disease severity, change in liver growth within individuals and (serious) adverse events. The study is designed as a prospective open-label study with blinded endpoint assessment (PROBE).

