### MRI scans

Liver and kidney volumes (the latter in ADPKD patients only) will be measured using an MRI scan at screening, 6, 18, 24 and 36 months. MRI scans will be performed using a standardized protocol, including a coronal T2-weighted single-shot fast gradient spin-echo sequence with fat-saturation with a slice thickness of 3 mm which is the primary sequence to determine liver volumes. In addition, a transversal T2-weighted single shot fast gradient spin-echo sequence with fat suppression and a coronal T1-DIXON-VIBE spoiled gradient echo sequence will be obtained. After pseudonymization, MRI scans will be sent to the central reading facility, where images will be analyzed blinded for patient, time and treatment by trained observers using an automated MRI program [30]. To ensure that valid MR images are obtained, quality control will be performed within 72 h by trained personnel. In case a scan is rejected, it will be repeated.

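### The missing-data rule for the primary outcome normally turns a 6-month change into a full-weight annual rate, which is unbiased only if growth and treatment effect are linear over 18 months

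*Protocol article*

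**What the plan says.** All references are to the protocol article.

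- **Outcome.** Primary outcome defines "Liver growth (%/y), calculated over the first 18 months of the trial". The abstract also calls it an annualised rate.
- **Test.** Under Statistical analysis, growth is "compared between direct and delayed starters, an unpaired t-test will be used". Each patient supplies one value and no weighting is mentioned.
- **Missing data.** The same section continues: "In case of missing data, last information will be used adjusted for the duration of follow up".
- **Scans.** Under MRI scans, liver volume "will be measured using an MRI scan at screening, 6, 18, 24 and 36 months". Month 6 is thus the only scheduled follow-up scan before month 18.
- **Time course.** Exploratory outcomes lists acute against chronic effects on liver growth. Statistical analysis will explore the linearity of growth, and also "whether the liver growth rate during treatment is different in the first 6 months of treatment compared to the 12 months thereafter". The mixed model is reserved for that question.
- **Drop-out.** Sample size calculation allows for 20%. Under Criteria for withdrawal, patients who leave in the first 3 months are replaced and left out of the intention-to-treat analysis. Later leavers are not replaced.
- **Sensitivity analyses.** These are covariate adjustment, interactions, a breakpoint analysis in direct starters and a per-protocol analysis. None examines the missing-data rule.

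**The concern.** On a %/y outcome, adjusting the last information for duration most naturally means dividing the last observed change by the time it covers. A completer's change is divided by 1.5 y. A patient last scanned at month 6 has the change divided by 0.5 y, and both values then count equally in the t-test.

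That is harmless for the mean only if volume moves along a straight line and the treatment effect builds up evenly. The protocol treats a different effect in the first 6 months as an open question, yet its primary estimate takes the answer for granted whenever a month-18 scan is missing. At stake are the size of the reported effect and some of the power. A patient who leaves between months 3 and 6 also remains in the analysis set with no scheduled follow-up scan to annualise.

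**Working it through.** **Inputs from the article.** Control growth is 5.8% per 18 months with an observed SD of 2.8% ("the mean liver growth rate in patients meeting the inclusion criteria was + 5.8% ± 2.8% per 18 months"). The planning SD is 5.6% ("we conservatively doubled the SD to ensure enough power"). The target is zero growth, with power 80%, alpha 0.05 (sides not stated; two-sided used), 20% drop-out, N = 36 and 1:1 allocation. Per year, the effect is 5.8/1.5 = 3.87 %/y and the planning SD is 5.6/1.5 = 3.73 %/y.

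**Assumed, because the article does not give them.** The time course of the effect, how missing scans split between arms, and the error per scan.

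**1. The plan's own figure.** n per arm = 2 × (1.96 + 0.842)² × (5.6/5.8)² = 14.63, so 15 per arm and 30 in total. 30 × 1.2 = 36; dividing by 0.8 instead gives 38. The stated 36 is reproduced.

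**2. Weight of an imputed value.** The multiplier is 1/0.5 = 2 for a 6-month change and 1/1.5 = 0.667 for an 18-month change. The ratio is 3.

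**3. Bias.** Let A6 and A18 be the treatment effects on volume (%) at months 6 and 18, let p be the fraction of direct starters imputed from month 6, and let control growth be linear.

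- True effect = A18/1.5
- Estimate under the rule = (1 − p) × A18/1.5 + p × A6/0.5
- Bias = p × (2 × A6 − 0.667 × A18), which is zero when A18 = 3 × A6

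| Time course, p = 0.20 | True (%/y) | Under the rule (%/y) |
|---|---|---|
| Early only, A6 = A18 = -1% | -0.67 | 0.8 × (-0.67) + 0.2 × (-2) = -0.93 |
| Early only, A6 = A18 = -4% | -2.67 | 0.8 × (-2.67) + 0.2 × (-8) = -3.73 |
| Linear, A6 = -1.93%, A18 = -5.8% | -3.87 | -3.87 |
| Late only, A6 = 0, A18 = -5.8% | -3.87 | 0.8 × (-3.87) + 0 = -3.09 |

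An early-only effect is overstated by 2p = 40% whatever its size. A simulation of 8,000 trials with 18 per arm agrees. Its results match 4 of 18 imputed (22%): an early -2% gives -1.89 to -1.93 against -1.33, and the late-only case gives about -3.0. If 6 of 18 direct starters are imputed, the early -2% case gives (12/18) × (-1.33) + (6/18) × (-4) = -2.2. An estimator using both scans recovered the true value, within simulation error, in every scenario. Under a strict null the rule's simulated type I error was 4.6% to 5.2%.

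**4. Noise.** With error SD e per scan, a rate over T years carries error SD √2 × e/T. The observed 2.8% per 18 months already contains scan error, so √2 × e ≤ 2.8, or e ≤ 1.98%. About 2% is therefore a ceiling, unless scans here are less precise than in the trial that supplied the SD.

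The SD of an imputed value is √(3.73² − (√2e/1.5)² + (√2e/0.5)²), taking each patient's true rate as constant. Power is for 3.87 %/y with 18 per arm and 20% imputed.

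| | e = 1% | e = 2% |
|---|---|---|
| Error SD at 18 months (%/y) | 0.9 | 1.9 |
| Error SD at 6 months (%/y) | 2.8 | 5.7 |
| SD of an imputed value (%/y) | 4.59 | 6.51 |
| Overall SD, 20% imputed (%/y) | 3.92 | 4.43 |
| Power under the rule | 82.0% | 72.0% |
| Simulated SE: rule / completers / both scans | 1.33 / 1.43 / 1.32 | 1.49 / 1.41 / 1.34 |

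For comparison, power is 85.5% with nothing missing and 76.4% with completers only (14.4 per arm).

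**The case against.** The rule is a reasonable attempt to keep every patient. The planning hypothesis is that growth stops. If it stops at once, a 6-month rate of zero equals an 18-month rate of zero and nothing is distorted. The article plans to explore non-linearity; it does not assert it. At 1% scan error or less the rule has more power than dropping the patients, and a better estimator gains almost nothing in precision. All of this stands.

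A reader might infer that the rule must flatter leuprorelin, because patients who cannot tolerate it leave early and are credited with an inflated benefit. For example, suppose 3% shrinkage by month 6 is followed by regrowth at the untreated rate. Completers then show (-3 + 3.87)/1.5 = +0.58 %/y and imputed patients -6.0 %/y. With 20% imputed, the bias is 0.2 × (-6.58) = -1.3 %/y, or 34% of the planned effect. The documents do not support this as a forecast. They plan for stopped growth rather than shrinkage, give one drop-out figure not split by arm, and list withdrawal reasons, such as a transplant offer, that are not specific to direct starters. A late effect reverses the sign.

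Criteria for withdrawal also asks later leavers for some early end-of-treatment step. If that includes an MRI, the last scan may fall after month 6 and the multiplier shrinks; patients leaving between months 3 and 6 may then have a scan, though over a short interval. The article does not say whether it does.

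Leaving completers' 6-month scans out of the primary analysis is not an error, since the outcome is defined from baseline to month 18.

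What remains is that the rule extrapolates on an assumption the protocol questions, and no stated sensitivity analysis tests it.

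**Conclusion.** The point holds as a conditional one and should be fixed. Reading the rule as annualising is an inference, but the natural one for a %/y outcome. On that reading a patient last scanned at month 6 counts three times as much per percent of volume as a completer and carries three times the scan-error SD.

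The direction of any bias depends on an unknown time course: 40% too large for a purely early effect and about 20% too small for a purely late one, with 20% imputed. There is none under linearity or a strict null, so neither a fixed bias towards the drug nor an inflated type I error under that null is shown. The loss of precision is real but small at 1% scan error. It becomes material only near the 2% ceiling implied by the article's own SD. The sample size of 36 is not in question on this ground.

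**What to change.** Make the primary analysis a longitudinal mixed model of liver volume (for example log volume) on the screening, 6- and 18-month scans, with visit as a category and a treatment-by-visit term. Report the month-18 contrast, converted to percent and divided by 1.5, as the effect in %/y, without single imputation. Keep the annualised last-scan rule with the t-test as a sensitivity analysis. State whether the early end-of-treatment assessment includes an MRI.

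A patient with only a screening scan then stays in the model without an invented rate, and a 6-month scan informs month 18 only as far as the data support.

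The cost is a change of wording, since every scan is already planned. The downside is a model-based primary analysis that assumes missing at random.
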